### Sample size calculation

Sample size calculations were informed by the work of Clarke et al. (2013) who, based on a comprehensive review of the literature, conservatively estimated abstinence rates of 23% for the intervention group and 14% for the control group. With alpha of .05 one-tailed and a power level of at least .80, these estimates result in a desired sample size of 292, which we have rounded up to 300 participants. These estimates are considered conservative for two reasons. First, whereas participants in the study by Clarke et al. (2013) did not receive any cessation support from prison authorities, prisoners in Queensland receive a week’s supply of free nicotine patches upon incarceration, associated with long-term smoking abstinence (Stead et al., 2012; Wu et al. 2006). Second, the observed intervention effect in the study by Clarke et al. (2013) was larger than expected (25% vs. 7% at 3 weeks), and the intervention in this trial is an enhanced version of the WISE intervention.

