## Methods

### Study Design

The study is a randomised controlled trial comparing two groups of soon-to-be released male prisoners. Three hundred sentenced prisoners will be recruited from four correctional centres in Queensland. Intervention group participants will take part in four group sessions of CBT and MI encouraging smoking abstinence post release, in the 4 to 6 weeks prior to release from prison. The comparison group will receive usual care plus a pamphlet encouraging smoking abstinence and a brief verbal explanation of the pamphlet at baseline. After individual baseline screening interviews assessing smoking history and future smoking intentions, participants will be randomised 1:1 to the intervention or comparison group. Once participants are released from custody, parole officers will record their self-reported smoking status at every appointment, for a maximum of 3 months. The primary outcome is point-prevalence of tobacco smoking abstinence at 1 month post-release. This study has been approved by the Griffith University Human Research Ethics Committee and by the Queensland Corrective Services (QCS) Research Committee. The trial is registered with the Australian New Zealand Clinical Trials Registry (ACTRN12616000314426) (Fig. 1).

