### Planned Analyses

For the primary outcome, the primary analysis will be an intention to treat analysis, with a *p*-value of <0.05 from a one-tailed chi square test of proportions considered statistically significant. The secondary analysis will be a per protocol analysis, excluding intervention group participants who did not attend at least three of the four intervention sessions. Secondary outcomes will be examined using chi square tests (for categorical variables), independent samples t-tests (for continuous variables) and discrete time survival analysis (for time to relapse).

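### The stated sample size of 292 (rounded to 300) does not follow from its own inputs: 460 men are needed, and 300 give about 64% power, not at least 80%

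*Protocol article*

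**What the plan says.** All inputs are in the article.

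- **Rates** (Sample size calculation): the planning values are taken from the earlier US trial, whose authors "conservatively estimated abstinence rates of 23% for the intervention group and 14% for the control group".
- **Error rates and result** (same section): "With alpha of .05 one-tailed and a power level of at least .80, these estimates result in a desired sample size of 292". This is then rounded up to 300 participants.
- **Total or per arm** (Study Design): "Three hundred sentenced prisoners will be recruited from four correctional centres in Queensland". Recruitment and inclusion criteria repeats this total, and Study Design and Randomisation both give 1:1 allocation. The design is therefore 150 men per arm. Nowhere is 292 or 300 described as a per-arm number.
- **Test** (Planned Analyses): the primary comparison uses p<0.05 "from a one-tailed chi square test of proportions considered statistically significant", which matches the sidedness of the sample size statement.
- **Claim of conservatism** (Sample size calculation): two reasons are given. One is that Queensland prisoners receive a week's "supply of free nicotine patches upon incarceration, associated with long-term smoking abstinence". The other is that the earlier trial observed a larger effect than it had planned for, 25% against 7% at 3 weeks.

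**The concern.** A total of 292 is small for a 9-point difference between rates of this size. The article gives both rates, alpha, sidedness and power, so the figure can be checked without any assumption from outside.

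What is at stake is the power of the primary analysis. A reader is told that an effect of the planned size would be detected at least four times in five. If that is not so, a non-significant result is weaker evidence against the intervention than the article implies. This matters because, by the article's own account, only one randomised trial of such an intervention came before this one.

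The patch argument belongs to the same paragraph. It is offered as a reason why the planning rates are cautious, but both arms receive the patches.

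**Working it through.** **Inputs.** p1 = 0.23, p2 = 0.14, one-tailed alpha 0.05 and power 0.80 (Sample size calculation); 1:1 allocation and 300 in total, so n = 150 per arm (Study Design, Randomisation).

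**Formula (pooled, no continuity correction).** Per-arm n = (z_alpha·A + z_power·B)² / d², where

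- d = 0.23 − 0.14 = 0.09, so d² = 0.0081
- mean rate = 0.185, A = √(2 × 0.185 × 0.815) = 0.5491
- B = √(0.23 × 0.77 + 0.14 × 0.86) = √(0.1771 + 0.1204) = 0.5454

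**Step 1: attempt to reproduce 292 as stated (one-tailed).** (1.645 × 0.5491 + 0.842 × 0.5454)² / 0.0081 = 229.1, so 230 per arm and **460 in total**.

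**Step 2: other formulas and the two-sided test.**

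| Formula | One-tailed 0.05: per arm (total) | Two-sided 0.05: per arm (total) |
|---|---|---|
| Pooled | 230 (460) | **292** (584) |
| Unpooled or arcsine | 228 (456) | 289 (578) |
| Continuity-corrected | 251 (502) | 313 (626) |

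No one-tailed variant gives 292, either per arm or in total. The pooled two-sided calculation gives 291.0, which rounds up to 292 per arm.

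**Step 3: power of the planned design.** z = (d√n − z_alpha·A) / B.

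- n = 150 per arm: (0.09 × √150 − 1.645 × 0.5491) / 0.5454 = (1.1023 − 0.9033) / 0.5454 = 0.365, so power is **64.2%**. Exact binomial enumeration of the one-tailed chi-square test gives 64.4%. With a continuity correction, or Fisher's test, it is 59.1%.
- n = 146 per arm (292 in total): 63.2%.
- A two-sided test with 150 per arm: 51.9%.
- For comparison only, 300 per arm would give 88.5% one-tailed.

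**Step 4: what 150 per arm can detect.** One-tailed, with 14% in the comparison arm, power reaches 80% at about 25.4% in the intervention arm (80.1%), a difference of 11.4 points.

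**Step 5: the patch argument.** Suppose, for illustration, that patches raise comparison-arm abstinence from 14% to 20%. One-tailed power with 150 per arm then depends on what stays constant:

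| Held constant | Rates | Power |
|---|---|---|
| Difference of 9 points | 29% vs 20% | 56.7% |
| Odds ratio, (0.23/0.77)/(0.14/0.86) = 1.83 | 31.4% vs 20% | 73.5% |
| Risk ratio, 0.23/0.14 = 1.64 | 32.9% vs 20% | 81.3% |

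The article fixes no effect scale, so patches could lower or raise power relative to 64%.

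**The case against.** The strongest defence is that the authors call 23% against 14% cautious and cite 25% against 7% at 3 weeks, close to this trial's 1-month endpoint. With 150 per arm, that effect gives power above 99%. Even the planned 9-point difference, set on the observed 7% comparison rate (16% against 7%), gives 79%. This stands as far as it goes: the trial may well have adequate power for an effect that the authors think plausible. It does not rescue the statement, which says that 23% against 14% leads to 292. The article also gives reasons why the contrast could be smaller here. The comparison arm gets a smoking-specific pamphlet with a verbal explanation instead of a general health film, and some contamination between arms is expected.

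Reading 292 as a per-arm figure does not help, because the article recruits 300 in total.

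Three stronger readings are tempting, but the article does not support them.

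- *That 292 is known to be a two-sided per-arm size mistaken for a total.* The match is exact, but only with the pooled, uncorrected formula, and the article names neither formula nor software. It is a likely explanation; the shortfall does not depend on it.
- *That the patch argument points the wrong way.* This holds only at a fixed absolute difference. On either relative scale, power rises. The supportable point is narrower: patches reach both arms, so they do not by themselves show that the assumed between-arm difference is conservative.
- *That losses push power lower still.* Men lost to follow-up count as non-abstinent, but the article expects low attrition and does not say whether the borrowed rates already count losses this way. A further deduction might count them twice.

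**Conclusion.** The sample size statement is wrong as written. Its own inputs require 230 men per arm, 460 in total, so the planned 300 is 160 short. Power at 150 per arm is about 64%, some 16 points below the stated minimum. The chance of missing the planned effect is about 36%, against the 20% implied.

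This rests only on figures in the article and on the planned one-tailed chi-square test without continuity correction; the choice of formula does not alter the conclusion. The 64% makes no allowance for contamination or for clustering within therapy groups, both of which would tend to lower it.

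The finding concerns the stated planning case. A reader might infer that the trial is underpowered for any plausible effect, but the earlier trial's observed rates, if they held here, would be detected almost surely.

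**What to change.** Keep 300 and restate the result in the sample size paragraph, for example: *With 150 per arm and one-tailed alpha .05, power is about 64% for 23% vs 14%, and 80% for about 25.4% vs 14%.*

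Qualify the patch argument: say that patches are given in both arms and that their effect on power depends on whether the absolute or the relative effect is expected to carry over. The observed 25% against 7% may stay as the reason for expecting a larger effect, provided that it is kept apart from the calculation for 23% against 14%.

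Read a non-significant primary result against the corrected power.

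The cost is one reworded paragraph and a less favourable stated power. No extra participants and no change to the planned test are needed.

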### Randomisation

After baseline assessment, each participant will be randomised 1:1 to the intervention or comparison group. Randomisation will be stratified by prison. The number of participants in each group per prison will reflect the sample distribution across the four prisons. Randomisation will also be stratified by intention to quit, given evidence (Thibodeau et al. 2010) that prisoners who have an intention to quit are more likely to remain abstinent post-release. The randomisation list will be divided into randomly permuted blocks of size 4, 6, or 8. Within each block, an equal number of intervention and comparison conditions will be assigned. Use of random permuted blocks ensures balance during assignment and helps to prevent participants from guessing which condition they have been assigned to (Beller et al. 2002). At this stage, the number of prisoners who intend to remain abstinent from smoking after release is unknown.

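### The primary chi-square test ignores the two randomisation strata, so it is slightly conservative and gives up a little power if intention to quit is prognostic

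*Protocol article*

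**What the plan says.** The Randomisation section names two stratification factors: "Randomisation will be stratified by prison" and "Randomisation will also be stratified by intention to quit". The reason given for the second is evidence that "prisoners who have an intention to quit are more likely to remain abstinent post-release". Balance is enforced by blocking: "The randomisation list will be divided into randomly permuted blocks of size 4, 6, or 8", with equal numbers per arm in each block. The section adds that "the number of prisoners who intend to remain abstinent from smoking after release is unknown".

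Planned Analyses states that for the primary outcome "the primary analysis will be an intention to treat analysis", with a p-value below 0.05 from a "one-tailed chi square test of proportions considered statistically significant". It names no stratified test, covariate or adjustment for this comparison.

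The Sample size calculation section rests on "abstinence rates of 23% for the intervention group and 14% for the control group", at one-tailed alpha 0.05 and power of at least 0.80. It gives 292 participants, rounded up to 300.

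**The concern.** Blocking within strata makes the arms nearly identical in their mix of prisons and intentions. Differences in abstinence between strata then contribute almost nothing to the chance variation of the arm difference. The unstratified chi-square still counts those differences in its standard error, so the standard error is a little too large whenever a stratification factor is related to the outcome. The protocol says that intention is so related, and that is its reason for stratifying on it.

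What is at stake is efficiency. The primary test would use less information than the design collects, and the remedy is only a change of wording. Naming the test now also avoids a later choice between adjusted and unadjusted results.

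**Working it through.** **Inputs from the protocol.** Rates 23% and 14%; one-sided alpha 0.05; 300 participants randomised 1:1, so 150 per arm; four prisons; balanced blocks within strata.

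**Assumptions not in the protocol.** Intention has two levels; 30%, 50% or 70% of participants have it; its odds ratio for abstinence is 1 to 10; prisons are equal in size, with a standard deviation of prison log-odds of 0 or 0.3; outcomes are independent within arms.

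**The plan's own figure first.** n per arm = [1.645·√(2·0.185·0.815) + 0.842·√(0.23·0.77 + 0.14·0.86)]² / 0.09² = 229.1, so 230 per arm and 460 in total. The stated total of 292 is not reproduced. With 1.96 in place of 1.645 the formula gives 291.0, so 292 *per arm*. At 150 per arm, one-sided power is Φ[(0.09 − 1.645·0.04484)/√((0.1771 + 0.1204)/150)] = 64%, where 0.04484 = √(2·0.185·0.815/150). This is the baseline for the comparison below.

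**One case by hand: odds ratio 3, half with intention.** Holding the overall rates at 14% and 23% gives comparison rates of 20.2% and 7.8%, and intervention rates of 32.3% and 13.7%.

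- *Level.* Variance used by the chi-square under the null: 0.14·0.86 = 0.1204. Variance that remains within strata: ½(0.2021·0.7979) + ½(0.0779·0.9221) = 0.1165. The ratio is 0.968, so the real one-sided level is about Φ(−1.645/√0.968) = 4.7%.
- *Power.* The true standard error of the difference is √[(0.1165 + 0.1685)/150] = 0.0436, where 0.1685 is the within-stratum variance in the intervention arm. The chi-square uses a null standard error of 0.0448 and has power Φ[(0.09 − 1.645·0.0448)/0.0436] = 64.5%. The stratified test uses √[2·½(0.2625·0.7375 + 0.1075·0.8925)/150] = 0.0439 and has power 65.8%. The gain is 1.3 points.

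**Simulation.** There were 20,000 trials per setting and eight strata (four prisons by intention). The planned chi-square was compared with a CMH test, both one-sided. Ranges are over the three shares and the two prison settings.

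| Odds ratio of intention | Power, chi-square | Power, CMH | Gain (points) | Level, chi-square |
|---|---|---|---|---|
| 1, no prison effect | 64–65% | 64–65% | about 0 | 0.051–0.053 |
| 2 | 64–65% | 65–66% | 0.4–1.0 | 0.048–0.052 |
| 3 | 64–66% | 65–67% | 0.8–1.7 | 0.046–0.050 |
| 5 | 65% | 67–69% | 1.3–3.5 | 0.041–0.048 |
| 10 | 65–66% | 67–73% | 2–7 | 0.037–0.047 |

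The CMH level stays between 0.047 and 0.054. Monte Carlo error is about 0.3 points for power and √(0.05·0.95/20,000) = 0.0015 for the level, so chi-square levels just above 0.05 are noise. The hand calculation agrees with its simulated counterpart without a prison effect (64.5% to 65.9%).

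**The case against.** The strongest reply is that this is a small matter. The sample size was computed from two overall proportions without adjustment, so nothing is lost against the power that was planned. Stratified allocation also has value for balance alone, and an unadjusted test keeps that value. At an odds ratio of 2 the level cannot be told apart from 5% and the gain is at most about one point. All of this stands, and it limits the weight of the point. It does not remove the mismatch. The article itself fixes the test, so the choice is not simply left to an analysis plan.

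A reader might infer four stronger things, none of which the document supports.

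- *That the primary test is invalid.* The departure from 5% is downwards, so false positives are not inflated by ignoring the strata.
- *That the gain is sizeable.* Comparison rates of 22% versus 6% by intention would give 1.6 points, and 26% versus 2% about 3.5. These imply odds ratios of (0.22/0.78)/(0.06/0.94) = 4.4 and (0.26/0.74)/(0.02/0.98) = 17. The protocol says only that abstinence is more likely with intention, and nowhere says that it differs by prison.
- *That ignoring the strata causes the low power.* The 64% follows from the sample size, which is a separate matter.
- *That intention modifies the effect of the intervention.* The protocol describes only an association with abstinence.

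**Conclusion.** The mismatch is real and its consequence is small. If intention to quit is prognostic, as the protocol says, the fixed primary test is mildly conservative and loses a little power relative to a test stratified by the randomisation factors. The loss is about 0.4 to 1.7 points for an odds ratio of 2 to 3, about 1.3 to 3.5 for 5, and 2 to 7 for 10. With no association there is no loss. In none of these settings does stratifying the test bring 300 participants to 80% power.

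The sizes depend on an assumed odds ratio and an assumed share with intention, neither of which the protocol gives. They also assume independent outcomes. The intervention is delivered in groups of four to six, and any clustering in that arm would push the type I error the other way. The quoted levels therefore show the effect of ignoring the strata only.

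**What to change.** In Planned Analyses, make the primary intention-to-treat test a one-sided Cochran-Mantel-Haenszel test stratified by prison and intention to quit. Report the stratum-adjusted risk difference with a confidence interval, and keep the unadjusted chi-square as a sensitivity analysis.

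If an adjustment for clustering in the intervention groups is also adopted, use instead one regression model with both stratification factors as covariates, because a standard CMH test cannot carry a cluster term.

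The cost is a change of wording. Prison is known, and the baseline assessment records post-release smoking intentions before allocation, so no new data are needed. The one drawback is that some strata may be sparse if few prisoners fall in one intention group. The CMH test tolerates this.

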### Measures

The baseline assessment will be administered individually to all participants and will take 15–20 min to complete. It measures participants’ smoking history, overall health status, drug use history, nicotine dependence (using the Fagerström Test for Nicotine Dependence; Fagerstrom & Schneider, 1989), and post-release smoking intentions and desires. The assessment was designed by the authors and informed by previous research (e.g. Clarke et al., 2011, 2013; Richmond et al. 2013a, 2013b).

Once participants have been released from prison, parole officers will assess participants’ self-reported smoking status at each appointment, using four questions: 1) Have you smoked since release? 2) If yes, how many weeks ago did you first smoke? 3) Are you currently smoking? 4) If yes, how many cigarettes do you smoke on average per day? In this way, absolute smoking status, duration of smoking abstinence, and intensity of the relapse (e.g., quantity of cigarettes smoked per day) can be measured. These questions also account for situations where a participant may have had a ‘lapse rather than a relapse’ (e.g., temporarily resumed smoking, then returned to abstinence).

Most parolees meet with their parole officers weekly, but some meet fortnightly or monthly. Parole officers will assess parolees’ smoking status at every meeting, but all participants will be assessed at 1 month post-release (the primary endpoint). Parole officers will continue to ask these four questions at each meeting with the participant for up to 3 months post-release. The rationale for a 3-month end point is that the majority of smoking relapses occur within the first 3 months post-release (Ockene et al., 2000). Clarke et al. (2013) also support this relatively brief follow-up period due to the high relapse rates immediately after release. Although restricting the study to parolees may have implications for generalisability, this is offset by an expected low rate of attrition, since most parolees are expected to attend most of their parole meetings.

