### Outcomes

The primary outcome of this study is point-prevalence tobacco abstinence at 1 month post-release, measured by self-report. Secondary outcomes include number of weeks to first cigarette after release, amount of tobacco consumed in the event of relapse, and point-prevalence of tobacco abstinence at 3 months post-release. Participants lost to follow-up will be considered non-abstinent—the most conservative assumption.

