Although this will be, to the best of our knowledge, the second ever randomised trial of an intervention to promote smoking cessation after release from prison, the protocol has some limitations. First, the trial is unblinded, but given the nature of the intervention and the follow-up, blinding is not feasible in this setting. Second, we note that some degree of contamination between the intervention and comparison groups in the prison setting is likely, but is unfortunately unavoidable in this situation. The consequence of any contamination would be to attenuate the intervention effect, such that the trial would be a conservative test of the intervention. Third, given high rates of reincarceration among ex-prisoners in Australia (Steering Committee for the Review of Government Service Provision, 2016), some proportion of participants may return to prison during follow-up. By making our primary endpoint only 1 month post-release we aim to minimise this form of potentially biased attrition. Fourth, the results may not be generalisable to all ex-prisoners, including to important subgroups such as women, people with an intellectual disability, ex-prisoners not on parole, and remandees (pre-trial detainees). Fifth, we rely on parole officers to collect follow-up data, which is likely to substantially reduce loss to follow-up but, despite the fact that tobacco smoking is not a prohibited behaviour for parolees, may impact on the data quality where good rapport cannot be established between parole officers and parolee participants. Sixth, our outcome will be measured by self-report, without biological verification. Although there is a possibility of self-report bias, tobacco smoking is not prohibited for parolees, and studies using both self-report and tobacco abstinence validation tests (e.g. presence of cotinine in urine) show that self-report can be a reliable measure of smoking abstinence (Clarke et al., 2013; Richmond et al., 2013b; Short et al., 2009).

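### The four follow-up questions cannot give point-prevalence abstinence over a defined period, so the 1-month primary outcome appears to rest on how a man labels himself

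*Protocol article*

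**What the plan says.** The protocol article defines the primary outcome twice. Outcomes says "The primary outcome of this study is point-prevalence tobacco abstinence at 1 month post-release, measured by self-report", and Study Design says "The primary outcome is point-prevalence of tobacco smoking abstinence at 1 month post-release". Neither gives a look-back period or names the answer that counts as abstinent.

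Measures prints the four items that parole officers ask at each appointment. The first three are "1) Have you smoked since release? 2) If yes, how many weeks ago did you first smoke? 3) Are you currently smoking". The last is "4) If yes, how many cigarettes do you smoke on average per day". The same section says that the items allow for a man who "temporarily resumed smoking, then returned to abstinence", but it sets no minimum smoke-free time for that return. On visit frequency it says "Most parolees meet with their parole officers weekly, but some meet fortnightly or monthly", with everyone assessed at 1 month.

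Outcomes adds "Participants lost to follow-up will be considered non-abstinent". The Discussion acknowledges that the trial is unblinded and that "our outcome will be measured by self-report, without biological verification".

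**The concern.** Point prevalence means abstinence over a stated recent period. No item asks about such a period, and none asks when the man last smoked. A man who smoked the day before his visit and regards it as a lapse can truthfully say that he is not currently smoking. Another man with the same history can say that he is.

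If the looseness is shared by both arms, it raises both recorded rates, narrows the difference and costs power. If it differs between arms, it biases an unblinded, self-reported comparison. The limitations in the Discussion concern whether men report truthfully. This problem would remain if every man did.

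**Working it through.** **What each item can deliver**

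| Item | Information | Point prevalence over a fixed window? |
|---|---|---|
| 1 | Any smoking since release | No: a no is continuous abstinence |
| 2 | Weeks since the first smoke | Only if the first smoke falls inside the window |
| 3 | Smoking currently, no period given | No: the period is left to the respondent |
| 4 | Average cigarettes per day | No: an amount, asked after a yes |

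**Who is affected.** A no to question 1 means abstinent over any window since release. A yes to question 3 means smoking. That leaves yes to question 1 with no to question 3. If question 2 puts the first smoke inside the window, the man smoked in the window. If the first smoke was earlier, his status in the window is unknown, because the last smoke is not dated. This is also the pattern by which the instrument identifies a lapse followed by a return to abstinence.

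**Size, as an illustration**

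Inputs from the documents: abstinence 23% and 14%, alpha 0.05 one-tailed, 300 men in total (Sample size calculation), allocated 1:1 (Randomisation), so 150 per arm. Assumed: a share *m* of non-abstinent men is recorded as abstinent. The documents give no value for *m*.

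*Plan's own figure.* Per-arm size = [z(1−α)·√(2p̄(1−p̄)) + z(0.80)·√(p1(1−p1) + p2(1−p2))]² / (p1−p2)², with p̄ = 0.185.
- One-tailed: (1.645 × 0.549 + 0.842 × 0.545)² / 0.0081, which rounds up to 230 per arm, or 460 in total.
- Two-tailed: the same formula with 1.960 gives 292 per arm, or 584 in total.

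The stated one-tailed total of 292 is therefore not reproduced. That is a separate matter. Here it only explains why the starting power below is 64% and not 80%.

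*Same relabelling in both arms.* Recorded rates are 0.23 + 0.77*m* and 0.14 + 0.86*m*, so the difference is 0.09(1 − *m*). Power is by exact enumeration of two binomials with the pooled z test, one-sided 5%.

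| m | Intervention | Comparison | Difference | Power |
|---|---|---|---|---|
| 0 | 23.0% | 14.0% | 9.0 points | 64% |
| 1% | 23.8% | 14.9% | 8.9 points | 62% |
| 2% | 24.5% | 15.7% | 8.8 points | 60% |
| 5% | 26.9% | 18.3% | 8.6 points | 55% |
| 10% | 30.7% | 22.6% | 8.1 points | 48% |

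*Different relabelling, no true effect (14% in both arms).* Each recorded rate is 0.14 + 0.86*m*, with *m* specific to the arm.

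| m, intervention vs comparison | Recorded rates | Rejection rate (nominal 5%) |
|---|---|---|
| 2% vs 1% | 15.7% vs 14.9% | 7.5% |
| 4% vs 2% | 17.4% vs 15.7% | 11% |
| 10% vs 5% | 22.6% vs 18.3% | 23% |
| 5% vs 10% | 18.3% vs 22.6% | 0.5% |

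**The case against.** **The link to question 3 is not stated.** No section says that question 3 defines the primary outcome, and the rule that turns answers into abstinent or not may sit in a full protocol or analysis plan. This stands: the link is an inference. It rests on question 3 being the only item that can separate point prevalence from never having smoked since release.

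**A later plan could use the other answers.** Visits are weekly for most men, so a change on question 1 between visits, or the answer to question 2, can place the first smoke in a recent interval. A plan could also adopt continuous abstinence from question 1. Both are true. A reader might infer that no analysis plan could help any man, and the documents do not support that. The gap is confined to the men isolated above. For them no rule can recover a last smoke that was not asked for, and men seen fortnightly or monthly have fewer interim answers to narrow it.

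**Tolerating lapses is a deliberate choice.** It is, and a 7-day rule would count some recent lapses as smoking. But the choice is incomplete without a minimum smoke-free time, so each respondent sets his own.

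**The illustration may overstate.** It relabels a share of all non-abstinent men. Those lost to follow-up are scored non-abstinent whatever they would have answered. The Discussion also cites studies in which the majority resumed smoking on the day of release, so many non-abstinent men may be plain current smokers. This stands, and it is why the range starts at 1%.

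**Two stronger readings are tempting.** One is that the looseness favours the intervention, because the sessions might make men readier to call recent smoking a lapse. The documents say nothing on this. Sessions about recognising triggers could equally sharpen reporting, and the last row of the second table shows the opposite effect. The other is that leaving out the word tobacco lets recent smokers pass as abstinent. It does not. Asking about smoking in general would, if anything, count non-tobacco smoking as smoking, and question 4 does name cigarettes.

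**Conclusion.** The concern holds in this form: the printed items cannot yield abstinence over a defined period, and the primary outcome appears, by inference, to depend on a self-label. Status within a fixed window cannot be derived for men who answer yes to question 1 and no to question 3 and whose first smoke came before the window. The documents do not show how many such men there will be.

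On assumed relabelling of 1% to 10% in both arms, the cost is roughly 2 to 16 percentage points of power from a base of 64%. With unequal relabelling and no true effect, rejection ranges from 0.5% to 23% in the cases shown. The direction is open, and the 23% is one chosen scenario, not an expected false-positive rate. The point merits a change because the outcome is primary, unblinded and unverified, and the remedy is small.

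**What to change.** - Add a question with a fixed look-back window, for example whether any tobacco was smoked in the past 7 days. It can replace question 3 or stand beside it. The length of the window matters less than fixing one.
- State in Outcomes that a no to this question at the 1-month assessment defines the primary outcome.
- Report a no to question 1 at 1 month as a continuous-abstinence sensitivity analysis.
- As a separate, minor edit to the same form, name tobacco in the items so that they match the stated tobacco outcome.

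The cost is one item on a short form and one sentence in Outcomes. Abstinence rates would be slightly lower in both arms, and some recent lapses would count as smoking. If follow-up has begun, answers obtained under the two versions must be kept apart, and forms already completed cannot be repaired. That is a reason to add the new question alongside question 3 and not in its place.
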